### Procedure for unblinding if needed {17b}

In this trial, no harmful procedures are introduced and adverse effects are unlikely. In the event that an adverse effect did occur, appropriate assistance will be provided by an expert in the field who is independent to the trial team. Therefore, unblinding will not be required in this trial.

## Data collection and management

### Plans for assessment and collection of outcomes {18a}

The outcomes will be assessed using validated questionnaires and physical examinations (Table 3).

A questionnaire to assess details of presenting complaint, demographic data and details of medical and surgical history will be administered by the lead researcher. Physical and social disabilities will be assessed by a trained physiotherapist using methods listed in Table 3. Participants’ perceptions of the effects of meditation on pain, physical disability and psycho-social disability will be assessed qualitatively using focus groups conducted by the lead researcher. Focus groups will be applicable only to a subset of participants, but we will take steps to ensure that the subset of participants is representative of the wider participant population (i.e. age, gender, age, pain rating).

The focus groups will be audio-recorded and transcribed verbatim. The transcriptions in Sinhala will then be translated into English.

Data collection forms can be obtained on request from the lead researcher.

The Oswestry Neck Disability questionnaire consists of 10 sections which include questions on pain intensity, personal care (washing, dressing, etc.), lifting objects, reading, headaches, concentration, work, driving, sleeping and recreation. Under each section, there are five responses graded from 0 to 5, whereby zero indicates no disability and five indicates the highest disability [22].

DASH consists of three sections which include questions on activities performed at home, work and during recreation. First section has thirty questions. Under each question, there are five responses graded from 0 to 5, where zero indicates no difficulty and five indicates extreme difficulty [23].

The SF-36 questionnaire has 11 sections which include questions on vitality, physical functioning, bodily pain, general health perceptions, physical role functioning, emotional role functioning, social role functioning and mental health. Under each section, the potential responses range from 1 to 6 with higher scores indicating less disability [24].

### Plans to promote participant retention and complete follow-up {18b}

Participants in the intervention groups will be taught meditation by an experienced meditation instructor during the first 8 weeks on a weekly basis. At the beginning of the study, participants will be educated on the nature and potential purpose of meditation, and that for any potential benefits of meditation to be realised, it is important that they practise their meditation on a regular basis for the required period of time. This intervention does not include any harmful or painful procedures; thus, adverse events are unlikely. Participants will be regularly monitored on a weekly basis, and if by any chance an adverse event does occur, they will be referred to the appropriate specialist.

### Data management {19} and Confidentiality {27}

Participants will be allocated a unique identification number at the beginning of the study. Participants will not be photographed or video-taped, but they will be audio recorded for focus groups. All identifiable data (names, addresses, contact details) and the main data will be encrypted and stored separately from each other in a secure folder that can only be accessed by the research team. A locked filing cabinet will be used to store non-digital data. The keys will be accessible only by the research team. Data will be protected for 10 years. The results published from this study will be in the form of data for the whole group. During the study, monthly checks will be conducted by the research team comparing the hard and soft copies to identify any missing data.

## Statistical methods

### Statistical methods for primary and secondary outcomes {20a}

Descriptive statistics (means, SDs, percentages, *T*-tests, chi-square tests) will be used to describe patient characteristics at baseline, differences between groups at baseline, and for all outcomes at each follow-up time point (4-, 8- and 12-week follow-up). The significance level that will be used is 5% (corresponding 95% confidence intervals will be presented) [26] and the SPSS statistical soft wear version 21 will be used in data analysis. If data is normally distributed, a two-way ANOVA will be used to explore any changes in the primary outcome between patients in the three intervention arms (Anapana, Body Scan and Metta) and the usual care control group between baseline and the 8-week follow-up. Similarly, any changes in secondary outcomes between the four arms (three intervention arms and the control arm) will be explored at 4- and 12-week follow-ups. If the data is not normally distributed, a nonparametric equivalent, such as Kruskal-Wallis, will be used.

Treatment effects (between group differences) will be presented with corresponding confidence intervals.

Multivariate linear regression will be used to explore any effect of the independent variables of age, gender, level of income, level of education, changes in the amount of medication used and the weekly, mean meditation duration on the primary outcome at 8-week follow-up and in the secondary outcomes at 4- and 12-week follow-up. However, because they are not assessing differences between treatment arms, multivariate regression analyses will only be exploratory.

All focus groups will be audio-recorded and transcribed verbatim and translated to English [27]. For the qualitative data analysis, the literature recommends a scientific model be used [27]. To do this, the Richie and Spencer model will be used as it provides a sound analytical model [27]. ATLAS.ti will be used to manage the analysis due to its usefulness for coding.

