### Sample size {14}

Sample size was calculated using the WinPepi version 11.65 statistical software. Results from a study by Jeitler et al. [11] with patients with chronic neck pain were used to calculate the sample size. In sample size estimation, we used the standard deviation values of the intervention group (17.2) and the control groups (21.5) after 8 weeks of treatment as stated in the study done by Jeitler et al. [11]. According to this study, the baseline pain value (45.5 SD 23.3) in the intervention group reduced to (21.6 SD 17.2) after 8 weeks of treatment and the baseline pain value (43.8 SD 22) in the control group reduced to (37.7 SD 21.5) after 8 weeks of treatment. Therefore, we considered 17.8 as the minimally important clinical difference. Using these values and a power of 80%, ratio of 1:1 and a significance level of 5%, the sample size was calculated. According to the calculation, the total sample size was 76 and number of patients for each arm of the trial was 19. According to an RCT conducted by Rantonen et al. [25] involving three intervention groups and a control group, the dropout rate was 26%. If we use this 26% dropout rate, and to maintain a total sample of at least 76, we need to have at least 26 patients per each arm of the trial. No adjustments will be made for multiple testing.

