### Study limitations

This is a four-arm parallel clinic-level randomised controlled trial. There can be issues related to clustering effects and allocation concealment. Therefore, allocation to a certain clinic day will be based on availability of sessions rather than patient characteristics, and all patients attending sessions on the relevant days will be systematically invited into the study. The similarity of study participants between intervention groups at baseline will be assessed.

In a randomised controlled trial, patients (or in this case clinic days) are randomly allocated to intervention or control arms. Therefore, patients may receive a meditation intervention that may not be the ideal technique for them personally. In this study, patients will be asked to meditate for at least 15 min/day on their own at home and record the practice duration in a logbook. Therefore, it will not be definitively possible to assess whether the meditation is actually performed or to assess the quality of meditation practised. Other limitations of the study is that analyses may be affected by imbalances between groups at baseline and the limited number of patients in each arm of the trial.

In the present study, expected loss to follow-up is high and potentially puts the study at risk of bias. To reduce dropouts in our study, the patients will be taught about the benefits of regular meditation prior to teaching them meditation. If patients experience any difficulty during their daily meditation practice, they have the facility to discuss them with the meditation instructor

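### Baseline t-tests and chi-square tests say little about similarity at 26 per arm, and the stated analysis of change has no baseline covariate to absorb an imbalance

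*Protocol article*

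**What the plan says.** Three parts of the protocol article bear on this.

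- **Statistical methods {20a}.** Descriptive statistics are to include t-tests and "chi-square tests) will be used to describe patient characteristics at baseline, differences between groups at baseline". The section then states: "The significance level that will be used is 5"%. The primary analysis is a two-way ANOVA of change in pain from baseline to week 8 across the four arms, or a nonparametric equivalent such as Kruskal-Wallis. No baseline covariate is named for it. Age, gender, income, education, change in medication and meditation time enter a separate regression, about which the section says: "However, because they are not assessing differences between treatment arms, multivariate regression analyses will only be exploratory".
- **Study limitations.** The authors concede possible problems with clustering and allocation concealment. They name three responses: patients reach a clinic day by session availability, all attenders on the relevant days are systematically invited, and "The similarity of study participants between intervention groups at baseline will be assessed". They also list as a limitation that "analyses may be affected by imbalances between groups at baseline and the limited number of patients in each arm of the trial".
- **Sequence generation {16a}.** Clinic days, not patients, are allocated to arms by lottery, and they are reallocated after 6 months.

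The article gives no other method for comparing the arms at baseline.

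**The concern.** A significance test asks whether an observed baseline difference is larger than chance would produce. It does not measure how alike the arms are, and with small arms a sizeable difference can easily be non-significant. When several variables are tested across four arms, some results will also be significant by chance.

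This matters more here than in an individually randomised trial. Only four clinic days are allocated at a time, so differences between arms are not limited to the chance variation expected when patients are randomised one by one. The protocol itself says that imbalance may affect the analyses, yet the primary comparison it states does nothing about a baseline difference once one is seen. The variables that could absorb it sit in a regression that, in the protocol's words, does not compare arms. At stake is the estimated difference in change in pain, the primary outcome.

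**Working it through.** **Inputs from Sample size {14}.** SDs at baseline are 23.3 and 22, and at week 8 "standard deviation values of the intervention group (17.2) and the control groups (21.5) after 8 weeks of treatment". The planned difference: "we considered 17.8 as the minimally important clinical difference". Power, ratio and level: "Using these values and a power of 80%, ratio of 1:1 and a significance level of 5%, the sample size was calculated". There are 19 per arm before and 26 per arm after allowing for 26% dropout. The pain values exceed 10, so they are not on the trial's own 0–10 scale; they are read here as 0–100. The percentages of 17.8 below do not depend on that reading.

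**Assumptions, not in the documents.** Two-sided tests (sidedness is not stated), the size of the true imbalance (0.3, 0.5 or 0.8 SD) and the correlation between baseline and week-8 pain (0.3, 0.5 or 0.7).

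**1. The plan's own figure.** The 17.8 is (45.5 − 21.6) − (43.8 − 37.7) = 23.9 − 6.1. Then

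n = (17.2² + 21.5²)(1.960 + 0.842)² / 17.8² = 18.78, which rounds up to 19 per arm, or 76 in total.

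19 / (1 − 0.26) = 25.7, which rounds up to 26. The stated sample size reproduces.

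**2. Chance that one pairwise t-test misses a true imbalance.** Noncentral t with 50 df and noncentrality d / √(2/26), two-sided 5%, 26 per arm:

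| True imbalance d | Missed |
|---|---|
| 0.3 SD | 81% |
| 0.5 SD | 58% (power 42.4%) |
| 0.8 SD | 19% |

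**3. All six pairwise tests read together.** By simulation (40,000 runs, 26 per arm):

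- One arm shifted by 0.5 SD: at least one of six tests is significant in about 69% of trials, so all six miss in about 31%.
- All arms balanced: at least one of six is significant in about 20%.

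**4. Smallest observed gap that reaches significance.** This needs no assumed true imbalance. The critical value is 2.009 × √(2/26) = 0.56 SD. Baseline pain SD is √((23.3² + 22²)/2) = 22.7, so the gap must exceed about 12.6 points, which is 12.6 / 17.8 = 71% of the planned difference. A 12-point gap in mean baseline pain would be reported as non-significant.

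**5. Effect on the difference in change.** Week-8 SD is √((17.2² + 21.5²)/2) = 19.5. If week-8 pain depends on baseline pain with slope b = r × 19.5 / 22.7, then with no treatment effect a baseline gap of 0.5 × 22.7 = 11.3 points shifts the difference in change by (1 − b) × 11.3 in size. The arm with more pain at baseline appears to improve more.

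| r | b | Shift (points) | Share of 17.8 |
|---|---|---|---|
| 0.3 | 0.26 | 8.4 | 47% |
| 0.5 | 0.43 | 6.5 | 36% |
| 0.7 | 0.60 | 4.5 | 25% |

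This takes the gap between arms to regress towards the mean as differences between patients within an arm do. A stable difference in pain level between the patients of different clinic days would not follow this pattern.

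**The case against.** A reader might infer that a non-significant baseline table will be used to declare the arms comparable and so clear a biased comparison. The documents do not support that. The tests are listed among descriptive statistics, next to means and SDs that would show an 11-point gap whatever its p-value. The limitations section says only that similarity will be assessed, and it openly lists imbalance as a limitation. Nor is similarity the sole safeguard: availability-based scheduling and systematic invitation stand beside it. The article also states sealed envelopes, the same physician and physiotherapist for all arms, and a second draw of clinic days after 6 months. All of this stands.

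It is also fair that 58% is the figure for a single pairwise t-test at one assumed imbalance. It does not carry over to chi-square tests or to six tests read together.

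Finally, covariate lists and imbalance thresholds are commonly left to an analysis plan, so their absence alone would be no finding. But the point here rests on what the article fixes: it names the baseline tests, names the primary analysis without a baseline covariate, and places the prognostic variables in a regression that it says does not compare arms. The objections remove the charge of false reassurance. They do not show that the tests are informative or that an imbalance, once seen, is dealt with in the estimate.

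**Conclusion.** The concern holds as a moderate one. Baseline significance tests at 26 per arm are a poor guide to similarity in both directions: a single pairwise test misses a real imbalance in 81% to 19% of cases over 0.3 to 0.8 SD, all six miss a 0.5-SD shift in one arm in about 31%, and six tests on a balanced variable raise a false alarm in about 20%.

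The more consequential part is the primary analysis. As stated it leaves a measured imbalance in the estimate: for a 0.5-SD gap in baseline pain, between 25% and 47% of the planned difference. Those percentages rest on the assumed gap, the assumed correlations and the regression pattern given in the working. They show what an imbalance would do, and do not predict that one will occur.

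**What to change.** In Statistical methods {20a}:

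- Make the primary between-arm comparison a model for week-8 pain adjusted for baseline pain and a short list of prognostic variables already collected (for example age, gender and education). Fix the list before any data are seen by arm, and use it whatever the baseline table shows.
- Remove t-tests and chi-square tests of baseline differences. Describe balance by means, SDs and standardised differences. Do not attach a pass/fail cut-off such as 0.25 SD: with four perfectly balanced arms of 26, at least one of the six pairwise differences would exceed it in about 81% of trials (40,000 simulations).

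In Study limitations, state that neither a balanced table nor adjustment rules out unmeasured differences under clinic-day allocation.

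The cost is wording and a few lines of code. No new data or patients are needed. The adjustment uses a few degrees of freedom with about 76 to 104 patients (4 × 19 to 4 × 26), so the list should stay short. Adjusting for baseline variables that predict week-8 pain should also improve precision.

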**Methods:**

This four-arm parallel clinic-level randomised controlled trial will be conducted with male and female patients aged 18–65 years, who are affected with chronic neck and shoulder region pain, and who attend one of four clinics held on four different days of the week in a single medical centre in the Colombo North region, Sri Lanka. Clinics will be considered as clusters and randomly allocated to intervention and control arms.

Data will be collected using validated questionnaires, clinical examinations and focus groups. To compare primary (differences in changes in pain (Numeric Pain Rating Scale) at 8 weeks) and secondary (differences in changes in pain, physical disability, range of movement and quality of life (SF-36) at 4 and 12 weeks) outcomes between groups, a two-way ANOVA will be used if data are normally distributed. If data are not normally distributed, a nonparametric equivalent (Kruskal-Wallis) will be used. Focus group transcriptions will be thematically analysed using the Richie and Spencer model of qualitative data analysis.

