### Outcomes {12}

Primary and secondary outcomes are stated in Table 2.

**Table 2 Tab2:** Primary and secondary outcomes

Primary outcome	Secondary outcomes
Differences in changes in pain in the neck and shoulder region at 8 weeks’ follow-up.	(i) Differences in changes in pain in the neck and shoulder region at 4 and 12 weeks’ follow-up.
	(ii) Differences in changes in the pain free active range of movement in the neck and shoulder region at 4-, 8- and 12-week follow-up.
	(iii) Differences in changes in quality of life with regard to activities of daily living, occupation and social activities with family and friends at 4, 8 and 12 weeks’ follow-up.
	(iv) To determine how patients in the three intervention groups feel about the effects of meditation on pain, physical and social disability with regard to activities of daily living, occupation and social activities with family and friends at 8 weeks’ follow-up.

Participants will be requested to report the pain intensity ratings from the previous 24 h using the Numeric Pain Rating Scale (range 0–10) [21] (Table 3) corresponding to:Pain level when they wake up in the morningLeast painWorst painWhile pain intensity was assessed three times across 24 h, the mean score across the three ratings will be used as the primary outcome.The pain intensity ratings need to be maintained daily.

**Table 3 Tab3:** Methods of measurement of outcomes

Outcome measure	Method of measurement
Level of pain	Numeric Pain Rating Scale, rated on a 0–10 scale [21]
Physical disability	Oswestry Neck Disability questionnaire [22], Disability of Arm, Shoulder and Hand (DASH) questionnaire [23], questionnaire to assess details of pain and demographic data, and clinical assessment of active range of movement of neck and shoulder joint [5]
Quality of life	The SF-36 Questionnaire Short Form [24]
Feelings on pain, physical disability and psycho social disability	This will be assessed qualitatively using focus groups.

Differences in quality of life will be assessed using the validated SF-36 questionnaire [24] (Table 3).

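### The primary two-way ANOVA has no stated second factor, its Kruskal-Wallis fallback is not its equivalent, and no analysis adjusts for baseline pain

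*Protocol article*

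**What the plan says.** **Primary test.** Protocol article, Statistical methods for primary and secondary outcomes {20a}: if the data are normal, "a two-way ANOVA will be used to explore any changes in the primary outcome between patients in the three intervention arms" "and the usual care control group between baseline and the 8-week follow-up". The Abstract (Methods) repeats it: "a two-way ANOVA will be used if data are normally distributed". Neither place names the two factors, and neither mentions a repeated-measures, mixed or within-patient term.

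**Fallback.** Same section: "If the data is not normally distributed, a nonparametric equivalent, such as Kruskal-Wallis, will be used". It does not say which data are to be checked or by what criterion. The paragraph that follows undertakes to report between-group differences with confidence intervals.

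**Outcome.** Outcomes {12}, Table 2, defines the primary outcome as "Differences in changes in pain in the neck and shoulder region at 8 weeks", so baseline enters by subtraction.

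**Covariates.** The only regression uses "the independent variables of age, gender, level of income, level of education, changes in the amount of medication used" and mean weekly meditation time. Baseline pain is not listed. The section calls this regression exploratory and says it does not assess differences between arms.

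**Baseline differences.** Study limitations concedes that "analyses may be affected by imbalances between groups at baseline". The only response there is to assess how similar the groups are.

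**The concern.** The primary model cannot be identified from the text. Two-way ANOVA over baseline and week 8 suggests arm and time as the factors. Run as an ordinary factorial, it treats a patient's two ratings as independent observations. Run as a mixed ANOVA, or on change scores, it does not. These analyses behave very differently, and on the change-score reading the second factor has no meaning at all.

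The fallback has a separate fault that holds on every reading. Kruskal-Wallis has one factor, no interaction and no covariate, so it cannot replace a two-way model, and it does not deliver the promised estimates. The choice between the two tests is left to a normality check of unspecified form with about 19 completers per arm.

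The best predictor of week-8 pain likely to be at hand, baseline pain, is used at most by subtraction. That costs precision in a small trial and leaves the comparison open to regression to the mean if the arms differ at baseline.

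**Working it through.** **Step 1: the plan's own figure.** Inputs from Sample size {14}: difference 17.8, week-8 SDs 17.2 and 21.5, power 80%, significance level 5% (two-sided assumed), ratio 1:1.

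- Pooled SD = √[(17.2² + 21.5²)/2] = 19.47.
- n per arm = 2 × (1.960 + 0.842)² × 19.47² / 17.8² = 18.8, so 19; four arms give 76.
- With 26% dropout: 19/0.74 = 25.7, so 26 per arm.

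The stated figures reproduce. Note that 17.8 = (45.5 − 21.6) − (43.8 − 37.7) is a difference in changes, whereas 19.47 is an SD of week-8 scores.

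**Step 2: the candidate analyses.** The protocol gives no baseline/week-8 correlation ρ, so 0.3, 0.5 and 0.7 are assumed. Simulation: four arms of 19, normal data, equal SDs at both visits, patients independent, one arm shifted by 17.8/19.47 = 0.914 SD, overall F test at 5%, 40,000 runs per setting.

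| | ρ = 0.3 | ρ = 0.5 | ρ = 0.7 |
|---|---|---|---|
| Ordinary factorial, arm × time: error rate | 1.1% | 0.2% | below 0.1% |
| Ordinary factorial, arm × time: power | 45% | 40% | 32% |
| Ordinary factorial, arm main effect: error rate | 11% | 16% | 20% |
| Change score or mixed ANOVA: error rate | 4.9% | 5.3% | 4.8% |
| Change score or mixed ANOVA: power | 65.9% | 81.3% | 96.5% |
| ANCOVA on baseline: error rate | 5.2% | 5.2% | 4.8% |
| ANCOVA on baseline: power | 84.9% | 91.2% | 98.3% |

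A separate run with 20,000 replicates under the null gave 15.4% for the arm main effect at ρ = 0.5, so about 15% is a fair summary. With 6,000 replicates per setting, shifting all three meditation arms instead of one gave almost the same power.

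The last contrast follows from the residual variances, relative to the week-8 variance: 2(1 − ρ) for the change score and 1 − ρ² for ANCOVA. These are 1.40 v 0.91, 1.00 v 0.75 and 0.60 v 0.51.

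**Step 3: the fallback.** In 1,500 runs (one arm shifted), Kruskal-Wallis on change scores had power of about 65, 77 and 95%; on week-8 scores alone, about 80, 78 and 78%. The protocol does not say which variable would be ranked.

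**Step 4: the same contrast with the protocol's quoted SDs.** The change-score variance in each group is SD₀² + SD₈² − 2ρ·SD₀·SD₈, using 23.3 and 17.2 (intervention) and 22 and 21.5 (control), averaged over the two groups. The ANCOVA SD is 19.47·√(1 − ρ²).

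| | ρ = 0.3 | ρ = 0.5 | ρ = 0.7 |
|---|---|---|---|
| Change-score SD | 25.1 | 21.3 | 16.8 |
| n per arm, change score | 32 | 23 | 14 |
| ANCOVA SD | 18.6 | 16.9 | 13.9 |
| n per arm, ANCOVA, difference 17.8 | 18 | 15 | 10 |
| n per arm, ANCOVA, difference 16.1 | 21 | 18 | 12 |

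The last row uses the raw week-8 difference, 37.7 − 21.6 = 16.1, as a cautious value. On either difference ANCOVA needs fewer patients. The planned 19 suits a change-score analysis only if ρ is about 0.6 (change SD 19.2).

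**The case against.** The strongest reply is that nothing in the protocol says the two visits would be treated as independent. The analysis is of changes, and Table 2 and the Abstract define the outcome as a difference in changes. A mixed ANOVA or a change-score analysis fits that wording, respects the pairing and holds its error rate at about 5%. This stands. A reader might infer that the planned test mishandles paired data or has the wrong error rate. The documents do not support that as a statement of fact; it is true only of the ordinary factorial reading. The inflated main effect also belongs to a test that does not address the stated outcome. Nor is baseline simply wasted: subtraction uses it, though inefficiently.

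The words introducing Kruskal-Wallis mark it as an example, and on change scores it is a valid test. That also stands, but it remains a one-way test with no estimate attached, and no companion estimator is named.

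A condensed article may leave a covariate list to a fuller document. However, this article states the primary test, the fallback and the switching rule, and it lists regression variables without baseline pain. Those statements can be judged as they stand. It would be too strong to say that the protocol expects baseline imbalance: Study limitations says only that it may affect the analyses.

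Finally, the simulation treats patients as independently randomised, whereas Sequence generation {16a} allocates clinic days. The figures therefore compare analyses with one another and do not predict this trial's power. If clinic-day populations differ systematically, ANCOVA can be biased too.

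**Conclusion.** The point holds as a badly fixed primary analysis, not as a demonstrated error-rate failure.

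Two parts are certain on any reading: the two-way ANOVA is not fully specified, and Kruskal-Wallis is neither its equivalent nor a source of the promised differences with intervals. The absence of baseline pain from every listed analysis is also plain from the text.

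The size is conditional. At ρ = 0.5, the readings open to an analyst range from about 40% power (ordinary factorial) to about 81% (change score or mixed), against about 91% for ANCOVA. On the favourable reading, the gain from ANCOVA is about 19, 10 and 2 percentage points at ρ = 0.3, 0.5 and 0.7. These figures rest on the assumed correlations, normal data, equal SDs, 19 completers per arm and no clinic-day effect.

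**What to change.** - State one primary analysis: ANCOVA of week-8 pain on arm and baseline pain. Report the adjusted differences between arms with 95% confidence intervals.
- Use the same model for pain at weeks 4 and 12 and for the quantitative secondary outcomes at each follow-up, each with its own baseline value.
- If residuals are skewed, keep the model and use robust or bootstrap intervals. Delete the normality-driven switch to Kruskal-Wallis, or keep that test only as a sensitivity analysis that cannot replace the primary result.
- Make the Abstract and section {20a} agree.

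Two additions should stay out of this change. Fixed clinic-day and period terms are not generally usable: with one arm per day and one redraw after 6 months, arm, day and period need 1 + 3 + 3 + 1 = 8 parameters for 8 day-period cells. They are jointly estimable in only 6 of the 24 possible redraws, and even then the cell means are saturated. Replacing week-8 pain by a mean of daily ratings ("The pain intensity ratings need to be maintained daily") would redefine the primary outcome after recruitment began. ANCOVA does not resolve allocation by clinic day, which is a separate issue.

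The cost is wording only, since Participant timeline {13} already schedules a baseline assessment. Because recruitment has started, the change should be recorded as a dated amendment before outcomes are examined by arm.

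### The exploratory regression of pain change leaves out baseline pain, so coefficients for practice time and medication change can be biased in either direction if those variables are related to starting pain

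*Protocol article*

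**What the plan says.** Under 'Statistical methods for primary and secondary outcomes', the protocol article plans a linear regression and describes it as exploring these effects: "age, gender, level of income, level of education, changes in the amount of medication used and the weekly, mean meditation duration on the primary outcome". It is planned for week 8, and for the secondary outcomes at weeks 4 and 12. The list has six variables. Neither baseline pain nor trial arm is on it, and no other section adds them.

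Table 2 under 'Outcomes' gives the primary outcome as "Differences in changes in pain in the neck and shoulder region at 8 weeks’ follow-up". The quantitative secondary outcomes in that table are also changes. 'Participant timeline' confirms that participants are assessed at baseline.

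The article limits the role of these models: "because they are not assessing differences between treatment arms, multivariate regression analyses will only be exploratory". The arms are compared separately: "a two-way ANOVA will be used to explore any changes in the primary outcome between patients in the three intervention arms" and the control group, with Kruskal-Wallis as the fallback.

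**The concern.** A change score contains the baseline value with a negative sign, so patients who start higher tend to fall further even when nothing acts on them. A predictor that is related to baseline pain, in a model without baseline pain, takes over part of that slope.

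Two listed variables could be related to baseline pain. Home practice is self-directed, so minutes may vary with severity in either direction. Pain medication is allowed as part of usual care, so the room to reduce or increase it may also depend on severity.

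This regression is the only statistical analysis that the article states for the practice and medication logs. The rationale for the trial rests partly on a short daily practice, so a finding that more minutes go with more relief would be a natural message to report. It could partly reflect who started with more pain. Equally, a real association could be hidden.

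**Working it through.** **The plan's own figures.** The article gives no figure for the regression, so the check starts from the numbers in 'Sample size'.

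- Intervention group of the cited trial: "the baseline pain value (45.5 SD 23.3) in the intervention group reduced to (21.6 SD 17.2) after 8 weeks of treatment".
- Control group: "the baseline pain value (43.8 SD 22) in the control group reduced to (37.7 SD 21.5) after 8 weeks of treatment".
- Difference in changes: (45.5 - 21.6) - (43.8 - 37.7) = 23.9 - 6.1 = 17.8, as stated ("we considered 17.8 as the minimally important clinical difference").
- Pooled SD = sqrt((17.2² + 21.5²)/2) = 19.47.
- n per arm = 2 × (1.96 + 0.842)² × 19.47² / 17.8² = 18.78, rounded up to 19. This matches. After dropout, 19/0.74 = 25.7, rounded up to 26, which also matches.
- Three meditation arms of 19 give the 57 patients used below.

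**How strongly change depends on baseline.** Let r be the baseline to week-8 correlation, which the article does not give. It is assumed to be 0.5 to 0.7.

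- SD of change = sqrt(SDb² + SDf² - 2·r·SDb·SDf)
- corr(baseline, change) = (r·SDf - SDb) / SD of change
- slope of change on baseline = r·SDf/SDb - 1

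| SDs used | r | SD of change | corr | variance explained | slope |
|---|---|---|---|---|---|
| Meditation, 23.3 to 17.2 | 0.5 | 20.9 | -0.70 | 49% | -0.63 |
| Meditation | 0.7 | 16.7 | -0.68 | 46% | -0.48 |
| Control, 22 to 21.5 | 0.5 | 21.8 | -0.52 | 27% | -0.51 |
| Control | 0.7 | 16.9 | -0.41 | 17% | -0.32 |

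**What a related predictor picks up.** Let rho be the correlation of the predictor with baseline pain, also not given and assumed. If the predictor has no effect of its own, its expected coefficient per SD is slope × rho × SDb. With the meditation SDs, r = 0.5 and rho = 0.3 this is -0.63 × 0.3 × 23.3 = -4.4 points in the cited trial's units. With the control SDs and r = 0.7 it is -0.32 × 0.3 × 22 = -2.1. At rho = 0 it is zero, and a negative rho reverses the sign.

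**False-positive rate.** Simulation with 57 patients, no true effect, baseline pain left out, r from 0.5 to 0.7:

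| rho | control SDs | meditation SDs |
|---|---|---|
| 0.1 | 5-7% | 7-8% |
| 0.2 | 9-11% | 16-18% |
| 0.3 | 15-20% | 33-36% |

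With all six predictors in the model, the meditation-SD rates are about 8-9%, 16-17% and 30-33%. At rho = 0 the rate is about 5%, and at rho = -0.3 it is the same size as at +0.3. With baseline pain added, it is about 5% throughout.

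**Why baseline pain alone is not enough.** The article does not restrict the regression to meditators, and control participants are asked not to meditate. The model was simulated with 76 patients, controls at zero minutes, a meditation effect of 17.8, no effect of minutes within arms, and an assumed coefficient of variation of 0.4 for minutes. Baseline pain was included but arm was not. Minutes were then falsely significant in roughly 84-96% of runs. With arm added, the rate returned to about the nominal 5%.

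**The case against.** The strongest reply is that the article declares these regressions exploratory and rests the arm comparison on a separate analysis. No primary conclusion or sample size depends on them. That stands and sets the severity. The label limits how strongly a result may be claimed, but it does not remove confounding from the coefficient.

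A reader might infer that regression to the mean will show up as an effect of minutes or medication. The documents do not support that. They give no correlation between either variable and baseline pain, so neither the size nor the sign of the bias is known. For medication the case is weaker still: patients in more pain may take more medication, but the listed variable is the change in amount, and only a generic predictor described as minutes was simulated.

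The meditation SDs give the high end. In that group the spread shrank from 23.3 to 17.2 while the mean fell by 23.9 points, so treatment response or floor effects may be mixed with regression to the mean. The control figures are the more cautious guide.

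'Outcomes' also says that the mean of three ratings serves as the primary outcome, so the dependent variable might be read as the week-8 score. Omitting baseline pain would still confound, but with the opposite sign, and the mechanism would not be regression to the mean. The simulated rates at n = 57 are then about 7-8%, 11-16% and 19-32% for rho of 0.1, 0.2 and 0.3.

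Finally, extra covariates for an exploratory model are often left to the analysis plan. Here, however, the article names a specific list, and the list is open to comment.

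**Conclusion.** The point holds as a minor one. The listed variables omit baseline pain, which is collected and, on the article's own SDs, strongly tied to change. Any listed predictor related to baseline pain would carry a biased coefficient, and the bias could create or mask an association. The false-positive rate is roughly 5-8%, 9-18% or 15-36% at predictor-baseline correlations of 0.1, 0.2 or 0.3 (control to meditation SDs, 57 patients), and nominal if there is no such relation. These figures rest on assumed correlations and on SDs from another trial's pain measure.

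A reader might also infer that the trial's main result is compromised. It is not: the comparison of arms does not use this regression.

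**What to change.** Add baseline pain to the regression for pain at each visit, and the baseline value of the same outcome to each secondary-outcome regression. In the same edit, include trial arm, or fit the practice-minutes model in the three meditation arms only with arm as a factor, so that minutes do not stand in for arm. State whether the dependent variable is the change or the week-8 score; with baseline pain in a linear model, the other coefficients are the same either way.

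The cost is a wording change, one degree of freedom for baseline, and three for arm (two if only the meditation arms are used). No new data are needed. Medication change is measured after allocation, so its coefficient should still be reported as descriptive.
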